**4.4.10 Data management and analysis**

At the end of each trail day, data will be collected, sorted and checked for consistency and for completeness. Open-ended questions will be categorized. All data collected will be entered in Epi-data soft ware package and exported to stata 8.2 soft ware package for more analysis. This analysis will be done in stages: univariate analysis ,where frequencies of variables will be generated and tabulated to establish the extent of use of these ANC services in the standard health centre setting compared to the second arm where extra education, and telephone remainders will be made. This level will also show the factors influencing timely return ANC visits, completion of the four recommended ANC visits, institutional deliveries and newborn care practices (Provision of warmth to the newborn, Initiation of breastfeeding within one hour of birth, Care for the cord and Immunization for the newborn-Polio 0 & 1; BCG within the neonatal period). At bi-variate level of analysis, cross tabulations will be run to establish associations between variables of interest. Chi-square tests will be used to establish significant associations. At multi variate analysis, all variables that will be found to be statistically significant at bi-variate ,will be subjected to the multivariate model (logistic) to control for confounding. The analysis will be run to get Odds Ratio values, 95%CI for the OR, and the respective p-values will be presented. Finally the primary outcomes of interest will be compared between the two arms i.e. a standard arm and the new trial arm upon which conclusions will be drawn.

*Quality Control*

To control quality of data to be collected,(completeness, correctness and consistency), the following measures will be undertaken:

Research assistants will be selected and trained by the principal investigator, questionnaires will be pre-tested for one day in a few selected health centres in Masindi and Kiryandongo. Completed questionnaires will be collected and checked by the principal investigator. Data collection will be carried out under strict supervision of the principal investigator. Data editing will be done and corrections will be made there at the selected health centres.

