## 4.3.8 Data collection and analysis plan

For both qualitative and quantitative data collection techniques research assistants familiar with the local dialect (Runyoro, Luo and Kiswahili) and possessing at least a degree in social sciences or public health having experience in social research will be recruited and trained for three days on the use of available tools and techniques. Pre-testing will be done twice to ensure suitability of the tools. Qualitative data from the Key Informant Interviews with elderly caregivers, TBAs and lactating women will be audio taped, transcribed verbatim and translated in to English, themes regarding prenatal and newborn homecare practices will be identified and described. A detailed description of the different care practices will be explored from elderly care givers and TBAs; these practices will be elaborated and broadly categorised according to prenatal, intra- and post-natal periods. The computer software program NVivo will be used. We will use content analysis to analyse data from TBAs and elderly caregivers and lactating mothers. Analysis will focus on making a detailed description of maternal and newborn care practices and the rationale for these care practices in the homes. For the In-Depth Interviews manual analysis of experiences of the different age groups adolescents (young adolescent ages 10-13 years; middle age 14-16 years and older adolescents ages 17-20) and older women over 20 years will be considered.

In the quantitative data with lactating mothers research assistants will be recruited and trained on the use of data collection tools; questionnaires will be pre-tested twice to ensue suitability of data collection tool; double data entry will be done in *epidata version 3.02*, cleaned and exported to *stata version 10.0* for analysis. Results will be presented in terms of descriptive statistics in proportions and rates. In a second level using bivariate data analysis, we will test for association between socio-demographic characteristics and the different maternal and newborn care practices using odds ratios and confidence intervals to test for levels of significance.

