### 4.4.8 Sample size

Using the formula for cluster randomised trials suggested by Hayes and Bennett ([Hayes and Bennett 1999](#_ENREF_36)),

**n = D(Z_α/2_ + Z_β_)^2^[π_0_(1- π_0_) + π_1_(1- π_1_)]/ (π_0 +_  π_1_)^2^** where

- **n** = number of participants in each arm,
- **D** = the design effect of 2.5,
- **Z_α/2_** = 1.96,
- **Z_β_ = 0.84,**
- **π_0_ =** current rate of institutional deliveries, 23.5%
- **π_1_** = estimated rate of institutional deliveries after the intervention, 33.5%

Substituting in the formula, we obtain a sample size of 788; allowing for a 10% loss-to-follow up we estimate a total population of 868 participants per arm. Further substituting in the formula for required number of cluster, C

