**C=1+(Z_α/2_ + Z_β_)^2^[π_0_(1- π_0_)/n + π_1_(1- π_1_)/n + k^2^(π_0_^2^ _+_ π_1_^2^)]/ (π_0 +_ π_1_)^2^**

Substituting for n=868, we arrive at a cluster number of 8 per arm; two arms will therefore require 1,736 participants distributed between 16 health centres; implying an average of 108 pregnant women enrolled per health centre for the entire four months. This will necessitate recruiting an average of 27 pregnant women per health centre per month.

This sample is based on the following assumptions:

- A degree of error, 0.05
- (95% confidence interval, **Z_a_** =1.96),
- the power to detect a significant difference between two comparison groups of 80% (**Z_a/2_** =0.84) to detect a 10% difference;
- **π_0_**, the current prevalence of institutional deliveries 23.5% ([DHO 2010](#_ENREF_28));
- **π_1_**, expected prevalence of institutional deliveries after the intervention 33.5% and
- A design effect **D,** 2.5 and
- Coefficient of variation between clusters of the same group **k_m_,** 0.25

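### Whole health centres are allocated and the sample size allows for clustering, but the named analysis does not, so a nominal 5% test has a true false-positive rate of about 21–26%

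*Protocol*

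**What the plan says.** Section 4.4.8 sizes the trial "Using the formula for cluster randomised trials", with "the design effect of 2.5", k = 0.25, two-sided 5% significance and 80% power to detect a rise in institutional delivery from 23.5% to 33.5%. It arrives at 868 women per arm in eight health centres per arm, about 108 women per centre. Section 4.4.9 assigns whole health centres to the arms, purposively and by location, although its subheading treats the women as the experimental units.

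Section 4.4.10 sets out the analysis in stages: frequencies, then cross-tabulations in which "Chi-square tests will be used to establish significant associations", then a logistic model containing the variables that were significant at the previous stage, reported as odds ratios with 95% confidence intervals and p-values. It closes by saying that the primary outcomes will be compared between arms, and names no further method. The abstract's paragraph on statistical analysis repeats the chi-square tests and odds ratios directly after listing the outcomes to be measured in the two arms.

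Neither place mentions clustering, a random effect, GEE, robust standard errors or a centre-level comparison.

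Sub-study two has a similar gap. Section 4.3.5 sizes it with a design effect of 2 for parish clusters. Section 4.3.8 then tests associations "using odds ratios and confidence intervals to test for levels of significance", again with no mention of the clusters.

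**The concern.** A chi-square test on 1,736 women assumes that each contributes independent information. Section 4.4.8 assumes the opposite: a design effect of 2.5 means that the variance of an arm's proportion is two and a half times what independence would give. Without that factor in the analysis, standard errors are too small, intervals too narrow and p-values too low. The direction is the same for every primary outcome that is positively correlated within centres. A difference that only reflects which centres fell in which arm could be reported as an effect of the intervention.

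The staged procedure carries the fault forward, because chi-square p-values decide which variables enter the logistic model.

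**Working it through.** **Inputs.** All are from section 4.4.8: p0 = 0.235, p1 = 0.335, z values 1.96 and 0.84, D = 2.5, k = 0.25, 8 centres per arm, about 108 women per centre (about 98 after 10% loss).

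**1. Reproduce the stated sample size.**
- p0(1 − p0) + p1(1 − p1) = 0.1798 + 0.2228 = 0.4026.
- n = D(1.96 + 0.84)² × 0.4026 / (p1 − p0)² = 2.5 × 7.84 × 0.4026 / 0.01 = 789 per arm. The protocol gives 788.
- 789 × 1.10 = 868, as stated.

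This uses the squared difference in the denominator. The formula is printed with a sum, which would give about 24.

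**2. False-positive rate of an unadjusted 5% test.** With variance inflation DE, the true rate is 2[1 − Φ(1.96/√DE)].
- With the stated D = 2.5: 1.96/1.581 = 1.240, giving **21.5%**.
- With k = 0.25, the intracluster correlation is k²p0/(1 − p0) = 0.0625 × 0.235/0.765 = 0.0192.
- 108 women per centre: DE = 1 + 107 × 0.0192 = 3.05, giving **26.2%**.
- 98 women per centre: DE = 1 + 97 × 0.0192 = 2.86, giving **24.7%**.

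**3. Check by simulation.** Beta-binomial data, 8 equal-sized centres per arm, 23.5% in both arms, 40,000 replicates:

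| Scenario | Chi-square on women | t test on 16 centre proportions |
| --- | --- | --- |
| D = 2.5, 108 per centre | 21.7% | 4.9% |
| k = 0.25, 108 per centre | 26.3% | 5.0% |
| k = 0.25, 98 per centre | 24.8% | 5.0% |

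**4. Confidence-interval width.** The shortfall factor is √DE.
- D = 2.5: √2.5 = 1.58.
- k = 0.25, 23.5% in both arms, 108 per centre: √3.05 = 1.75.
- k = 0.25, 23.5% against 33.5%, 108 per centre: the intracluster correlation at 33.5% is 0.0625 × 0.335/0.665 = 0.0315, so DE there is 1 + 107 × 0.0315 = 4.37. Weighting by each arm's binomial variance, (0.1798 × 3.05 + 0.2228 × 4.37)/0.4026 = 3.78, and √3.78 = 1.94.

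**5. Rejection rate when the effect is real (23.5% against 33.5%, simulated).**

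| Scenario | Chi-square on women | t test on centre proportions |
| --- | --- | --- |
| D = 2.5 | 94–95% | 73–77% |
| k = 0.25 | 91–92% | 59–60% |

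The higher chi-square figures are not usable power, because that test does not hold its 5% level.

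**The case against.** The strongest reply is that the text is silent rather than wrong. Section 4.4.10 says only that the model is logistic, and does not say how its standard errors are computed. The chi-square sentence there concerns associations in general and serves as a screen for the model, while the comparison of arms comes last with no test named. A separate statistical analysis plan could supply a cluster-adjusted variance.

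Part of this stands. That the logistic model is unadjusted is an inference from the absence of any cluster term. For chi-square no inference is needed: the protocol names the test itself, the abstract places it directly after the two-arm outcomes, and no alternative is offered for comparing arms. A named method that conflicts with the allocation is not a detail left for later.

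Four further limits stand:

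- The percentages apply to institutional delivery at 23.5% with equal centre sizes. The protocol gives no clustering figures for the other primary outcomes.
- The valid-test power of about 60% and the interval factor of 1.94 hold only under k = 0.25. Under D = 2.5 they are 73–77% and 1.58.
- Sub-study two is a survey, not the trial comparison. Its design effect of 2 was set for a prevalence and does not carry over directly to an odds ratio, so no figure is put on it here.
- The 5% error rate of the centre-level test assumes exchangeable centres. Sections 4.4.9 and 5.1 place centres by geography, and no clustering adjustment removes a difference between locations.

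**Conclusion.** The concern holds and must be fixed. The sample size and the analysis rest on contradictory assumptions about independence. Under the protocol's own clustering values, an ineffective intervention would be declared significant about one time in four or five instead of one in twenty: 21.5% at D = 2.5, and about 25–26% at k = 0.25 with 98 to 108 women per centre. The direction extends to any other primary outcome with positive within-centre correlation, but the size there is unknown. The objections limit how the figures are labelled; they do not remove the error.

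**What to change.** In section 4.4.10 and the abstract:

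- Remove chi-square as the test between arms.
- Make the primary comparison a centre-level analysis: an unpaired t test on the 16 health-centre proportions with 14 degrees of freedom. Add a two-stage version adjusted for covariates named in advance rather than screened by p-value.
- Alternatively, specify a logistic GEE or mixed model with health centre as the cluster and a named small-sample correction, since there are only 16 clusters.
- Report the observed intracluster correlation or k for each primary outcome.
- State that these methods correct the variance only, and that confounding by location remains because centres are assigned purposively.

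For sub-study two, as a secondary change, use survey methods with parish as the primary sampling unit.

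The cost is analysis wording and wider intervals, with no new data collection for this change. The t test needs no special software. If the model-based option is chosen, confirm that the Stata version used supports the correction, since the protocol names 10.0 in the abstract and 8.2 in section 4.4.10. A valid analysis will also show power below the planned 80% (73–77% under D = 2.5, about 60% under k = 0.25). Whether eight centres per arm is enough is a separate question for the sponsor.

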# Abstract

**Introduction**: Achieving targets for MDGS 4 and 5 in developing countries has proved elusive. Evidence suggests that a balance between preventive and health promotion interventions during the prenatal period can lead to consistent ANC utilisation and hence increased institutional delivery and reduction of maternal and neonatal mortality. In practice however, antenatal care is organised and delivered in favour of the technical clinical services dwarfing less technical health education interventions, as such, over 90% make first ANC visits but less than 40% make completed four visits, about 40% institutional delivery and less than 20% postnatal visits within six weeks. Evidence from Asia and Africa has demonstrated that community interventions with CHWs visiting individual pregnant women improve maternal and neonatal outcomes. Whether a combined package of prenatal education by CHWs at the primary health care facility and use of standardized mobile phones reminders to pregnant women can lead to improved selected maternal and neonatal outcomes in a low income setting is not known.

**Objective and Hypothesis**: This study aims at measuring the effect of standardized prenatal education interventions offered by Community Health Workers on uptake and utilisation of selected maternal and newborn healthcare services offered at the primary care facility to contribute to the reduction of maternal and neonatal mortality. This study is therefore designed to test the hypothesis that offering a package of standardized prenatal educational interventions at the primary healthcare facility combined with standardized telephone reminders targeting individual pregnant women can lead to timely return ANC visits, completed four ANC visits, increased institutional delivery and improved newborn homecare practices.

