# Chapter one

# Introduction and Background

Achieving targets for MDGS 4 and 5 in developing countries has proved elusive. Each year 340,000 women die due to pregnancy related causes, half of this being in Africa, while 4 million babies die within the first month of life and an equal number die as stillbirths ([Hogan M, Kyle J F et al. 2010](#_ENREF_40)). In Uganda, maternal mortality is estimated to be 435/100,000 live births while newborn mortality is estimated at 29/1000 live births translating to about 45,000 deaths in the first month of life ([MOH 2010a](#_ENREF_60)). Two thirds of these deaths could have been averted by interventions that are known to be cheap and effective ([Jones G SR, Black RE et al. 2003](#_ENREF_45); [Vishwajeet K, Aarti K et al. 2010](#_ENREF_94)), namely: creativity in health education and behaviour change communication ([Ronsmans C and Wendy J 2006](#_ENREF_79); [UNICEF 2009](#_ENREF_87)); institutional deliveries; healthy behaviours practiced at home and in the communities ([Lawn J, Pyande M et al. 2006](#_ENREF_52)).

Evidence suggests that consistent ANC utilisation leads to increased institutional delivery and reduction of maternal and neonatal mortality ([Ornella L, Seipati Mothebesoane-Anoh et al. 2006](#_ENREF_72); [WHO 2010](#_ENREF_113)). In most developing countries however, the picture is such that over 90% make first ANC visits, less than 40% make completed four visits, about 40% returning for institutional delivery and less than 20% postnatal visits within six weeks. In Masindi and Kiryandongo districts, for example, while first ANC attendance is about 90%, completed ANC visits is 30% and institutional deliveries 23.5% ([DHO 2010](#_ENREF_28)).

Improvement in institutional delivery requires a balance between preventive and health promotion interventions during the prenatal period. In practice however, antenatal care is organised and delivered in favour of the technical clinical services dwarfing equally important less technical health education interventions.

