### 4.4.9 Sampling procedure

Sixteen health centres in total will be proportionally selected from both Masindi and Kiryandongo district with Masindi contributing to 10 and Kiryandongo contributing to 6 HCs. A community trail involving two arms will be tried.

*Selection of the experimental units (pregnant women)*

Ten and six health centres will be proportionally selected from Masindi and Kiryandongo district giving a total of 16 heath centres in the trail.

From the 16 selected health centres, 8 of these will be purposively assigned to each of the two arms to minimize contamination. In each of the 8 health centres on each trial arm, 868 pregnant women with 28 weeks of pregnancy or below will be enrolled as they come in giving a total of 1736 in this trial. Health centres on two extremes of the districts will be assigned to either the intervention or the control group in order to avoid contamination between the two.

*Data Collection tools and procedures*

Semi-structured questionnaires written in English but administered in Runyoro will be used by research assistants.

*Training of research assistants*

Data collectors will be recruited and trained on data collection methods for two days. Training will include how to conduct individual interviews and data collection skills

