# Annex 15: SOPs: Standard Operating Procedure and intervention packages

### i) Standard operating procedure and intervention package for educational intervention during ANC

**(**[**Bhutta Z, Sajid S et al. 2011**](#_ENREF_10)**)**

When the pregnant women enter the clinic room

1. Identify pregnant women with all of the following conditions:
2. First visit of the current pregnancy,
3. Not more than 28 weeks of gestation
4. Administer the consent form
5. If she consents then open a file for her
6. Request for her ANC card
7. Enter all personal details available on the ANC card in to the file
8. Record any telephone contacts that you can use to access her in future

name, age, ethnicity, parity, LNMP, EDD, gestation age of the first visit, history of previous pregnancy outcome of the previous pregnancy (baby – alive or dead, mode of delivery), distance from the health facility, marital status, history of previous ANC attendance-Number of attendance, delivery (home, health facility, TBA etc).

Note the date for the next appointment, (all this information will be used to tailor the discussions)

-if she consistently attended all the expected milestones-then you find out what her motivation was to do so, and whether she plans to do the same for the current pregnancy;

- If not consistent-discuss the reasons for inconsistencies and help her to find a solution,

- diet during pregnancy-find out what foods are readily consumed and what she can easily afford, what foods could be prohibited during pregnancy (caution about antagonising cultures-you can find another acceptable alternative source of the food value) and discuss the importance for balances in diet, fruits, green vegetables, proteins and carbohydrates,

- Discuss work related activities-how much she does and who helps her with the routine household and garden chores.

- Discuss importance of ANC even when she has been attending consistently, the advantages of delivering in the health facility even when she has been delivering at the health facility,

- Birth preparation-clean clothes for the newborn (emphasis that clean does not mean new!-even old rages can be patched together washed clean, clean environment for the newborn,

- caring for the cord, dangers of applying substances to the cord,

- Pre-lacteal feeds-and its disadvantages-explain how breast milk eventually comes and the usefulness of colostrum.

- Discuss bathing of the new baby how soon and how to delay (delay up to 24 hours),

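### Choosing model variables by bivariate chi-square neither keeps arm in nor keeps post-enrolment variables out, so the adjusted arm odds ratio can be pulled toward 1 or left unreported

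*Protocol*

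**What the plan says.** Section 4.4.10 sets out a staged analysis. At the second stage, "cross tabulations will be run to establish associations between variables of interest" and "Chi-square tests will be used to establish significant associations". At the third stage, "all variables that will be found to be statistically significant at bi-variate ,will be subjected to the multivariate model (logistic) to control for confounding", and ORs with 95% confidence intervals and p-values are reported from that model. The section closes with "Finally the primary outcomes of interest will be compared between the two arms" and gives no method for that comparison. The Abstract repeats the staged plan. No covariate list appears, arm is not named as a fixed term, and no class of variable is excluded.

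Three other places bear on this.
- The Introduction says "Evidence suggests that consistent ANC utilisation leads to increased institutional delivery".
- The Abstract's hypothesis is that the package "can lead to timely return ANC visits, completed four ANC visits, increased institutional delivery and improved newborn homecare practices".
- Section 4.4.9 says of the 16 centres that "8 of these will be purposively assigned to each of the two arms to minimize contamination".

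**The concern.** The rule uses one screen for two tasks: finding factors associated with an outcome, and estimating the effect of the intervention. For the second task it can go wrong in three ways.

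(a) Timely return and four completed visits occur after allocation. On the protocol's own account the package raises them and they raise facility delivery. They are therefore open to selection in the delivery model, and adjusting for them removes the part of the effect that runs through attendance.

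(b) Arm is subject to the same screen as everything else. Adjusted arm ORs could then appear only for outcomes where the crude comparison was already significant.

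(c) A true confounder that misses p<0.05 is left out. Allocation is purposive, with centres at the districts' extremes placed in one arm or the other, so this model is the only confounding control described.

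The screen is also an ordinary chi-square test, although section 4.4.8 assumes a design effect of 2.5.

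**Working it through.** **Inputs from the protocol.** Facility delivery 23.5% against 33.5%, design effect 2.5, between-cluster coefficient of variation k = 0.25, 8 centres per arm, 788 women per arm before loss (section 4.4.8). Completed four visits: 30% (Introduction), 29.4% (section 4.1).

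**The plan's own figure.** 2.5 × (1.96 + 0.84)² × [0.235 × 0.765 + 0.335 × 0.665] / (0.335 − 0.235)² = 789, against the stated 788. This uses the difference of the rates in the denominator; the printed sum would give 24, which is a separate matter. The planning effect is therefore the 10-point difference, and its OR is (0.335/0.665)/(0.235/0.765) = 1.64.

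**(a) Adjusting for visits.** Assume completion rises from 30% by 10, 20 or 30 points and the visits-to-delivery OR is 1.5 to 4. Hold the total effect at 23.5% to 33.5% and solve for the arm OR given visits.

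| Rise in completion | Arm OR, visits OR 1.5 | Arm OR, visits OR 4 |
|---|---|---|
| 10 points | 1.58 | 1.47 |
| 20 points | 1.52 | 1.27 |
| 30 points | 1.46 | 1.10 |

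Check of the last cell:
- Control: 0.7 × 0.155 + 0.3 × 0.423 = 0.235.
- Intervention: 0.4 × 0.168 + 0.6 × 0.446 = 0.335.
- Arm OR among women without four visits: (0.168/0.832)/(0.155/0.845) = 1.10.

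Full mediation is the extreme. If delivery is 50% with four visits and 12.5% without, then 0.294 × 0.50 + 0.706 × 0.125 = 0.235. Reaching 33.5% needs completion of (0.335 − 0.125)/(0.50 − 0.125) = 56%. The adjusted OR is then 1.00 by construction. That case needs a visits-to-delivery OR of (0.50/0.50)/(0.125/0.875) = 7.

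**(b) Arm missing the screen.** Simulated ordinary chi-square test of arm, 8 centres per arm, 98 women per centre (788/8), centre rates normal with k = 0.25. Ranges cover repeated runs.

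| True difference | Arm not significant |
|---|---|
| 10 points | 9 to 10% |
| 7 points | about 26% |
| 5 points | 41 to 43% |
| 3 points | about 60% |

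**(c) Unclustered screening.** A centre-level variable unrelated to the outcome passes with probability P(|Z| > 1.96/√DE), where DE is the design effect.
- DE = 2.5: P(|Z| > 1.24) = 21.5%.
- DE from k = 0.25: the intracluster correlation is 0.25² × 0.235/0.765 = 0.0192, so DE = 1 + 97 × 0.0192 = 2.86, and the pass rate is about 24.7%.

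For woman-level variables the inflation is much smaller. DE 2.5 with 108 women per centre implies an outcome intracluster correlation of 1.5/107 = 0.014. If the covariate's own correlation is 0.05 to 0.20 (assumed), DE is 1 + 107 × 0.014 × 0.05 = 1.075 up to 1 + 107 × 0.014 × 0.20 = 1.30, and the pass rate is about 6 to 9%.

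**The case against.** Section 4.4.7 lists the visit measures as outcomes and arm as the independent factor, and section 4.4.10 gives confounding control as the purpose of the model. A sensible analyst could keep arm in and leave visits out. That stands in part: a reader might infer that visits will be adjusted for, but the text only fails to prevent it.

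A reader might also infer that the whole planned effect would vanish. The documents do not support this. It needs full mediation, while the protocol gives the package direct routes to delivery: reminders of due dates (section 4.4.5, phone SOP in Annex 15) and teaching on the advantages of facility delivery (section 4.4.6, Annex 15).

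Nor can one say the arm comparison may be missing altogether. The closing sentence of section 4.4.10 promises one for the primary outcomes. It states no method or adjustment, so it does not secure the adjusted OR.

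The high pass rate for noise variables applies at centre level. The details listed in the Annex 15 enrolment SOP are mostly woman-level, where inflation is modest.

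Finally, it is tempting to say that the needed covariates are already collected. The enrolment list, which includes "history of previous ANC attendance-Number of attendance, delivery (home, health facility, TBA etc", belongs to the SOP for the educational intervention. Annex 15 (iii) has community health workers (CHWs) entering and archiving those details, and Annex 9 says control centres have no CHW deployed. Capture in control centres is not established.

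**Conclusion.** The concern holds as a defect in a rule the protocol fixes. Followed literally, the rule can bias the adjusted arm OR toward 1, omit it, or leave confounding in it.

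The direction in (a) follows from the protocol's hypothesis that the package raises both visits and delivery. The size, 1.10 to 1.58 against 1.64, rests on assumed mediation strengths. The omission rates in (b) rest on the simulation set-up and k = 0.25. Point (c) has no computable size from the documents, but purposive allocation makes it important. Sample size is unaffected.

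**What to change.** In section 4.4.10, remove the significance screen from the effect analysis. For each primary outcome, specify one model with:
- arm always included;
- a short fixed set of pre-enrolment covariates recorded in both arms, for example age and parity, plus gestational age at first visit, previous place of delivery, previous antenatal attendance and distance if the enrolment file is also kept in control centres;
- no variable measured after enrolment;
- standard errors or random effects that account for the 16 health centres.

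Add district only if both arms are represented in each district, because assignment by geographic extremes may align district with arm. State that this model is the arm comparison promised at the end of the section. Present the factor screening separately as exploratory.

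The cost is a few sentences, a little more analysis work, wider intervals once clustering is counted, and a check that the enrolment file is completed in control centres. If it is not, baseline recording there has to be arranged before recruitment.
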